### Data collection and follow-up

Data on baseline characteristics and outcome variables are registered in the NPR, SHAR, and SFR. Follow-up will be performed postoperatively after 2, 5, and 10 years by linking between the registers (Table 1).

**Table 1 Tab1:** Content for the schedule of enrolment, interventions, and assessments

TIMEPOINT	STUDY PERIOD				
	Enrolment	Allocation	Post-allocation		
	*0*	0	*2y*	*5y*	*10y*
ENROLMENT:					
Eligibility screen	X				
Informed consent	X				
Randomization		X			
INTERVENTIONS:					
*Internal Fixation (control)*		X			
*Hip Arthroplasty (intervention)*		X			
ASSESSMENTS:					
*Baseline*	X	X			
*Primary outcome*			X	X	X
*Secondary outcome*			X	X	X

Primary outcome is a composite variable of reoperation rate and mortality

Secondary outcomes are: Reoperation rate, Mortality, PROM, Adverse Events, External validity

All outcomes will come from Registers

### Data quality assurance

The study progress and conduct will be monitored by a study coordinator before, during, and after the study concludes to ensure that all aspects of the protocol are adhered to in accordance with ICH-GCP guidelines and regulatory requirements. The register data will be automatically transferred to a study data base. Because the patient has a general right to protection against invasion of privacy, each patient will receive a unique identification number. The data will then be blinded correspondingly in all data analyses. However, the study monitor, auditor, representatives from any regulatory authority, as well as the appropriate ethical committee are permitted to review the patients’ data.

### Estimated sample size and power

The reoperation rate for hemiarthroplasty due to FNF is estimated at 5% according to reports from the SHAR [16, 17]. In recent registry based studies, patients with an FNF treated with THA had a significantly reduced risk of reoperation when compared with patients treated with hemiarthroplasty [18, 19]. Because we know that the variable “reoperations” does not have 100% completeness in the SHAR given that some procedures (e.g., debridement and irrigation or closed reduction) are not reliably registered, we assume that the actual reoperation rate is closer to 7.5%. The reported reoperation rates for uFNFs vary [6, 7, 20, 21], but we estimate that the rate is about 12.5% at 1 year after IF with screws/pins in older patients with uFNF. Mortality rates are reported from 11% at 1 year in a study with both displaced and undisplaced FNFs [22] to just over 20% in other studies [6, 8, 21].

In our primary outcome composite variable (reoperation rate and mortality), we expect a 15% 1-year mortality within the study cohort. We assume that death or reoperation would occur within 1 year in 27.5% (15% + 12.5%) of the patients in the control group (IF) and aim to detect a decrease to 22.5% (15% + 7.5%) in the intervention group (arthroplasty). We plan to include patients for 3 years. Patients will be censored at the time of reoperation or at time of death within 2 years, at time of withdrawal of informed consent or at the end of the study. The end of study will be when the last patient has a 1-year follow-up, cross-checking with the NPR has a 1 year delay for data completeness; hence, about two thirds of the patients will have a 2-year follow-up and the remaining patients between 1 and 2 years. Simulations under an assumption of constant hazard indicate that 1440 patients enrolled for 3 years, yielding about 586 events, would produce a power of 80% to detect such a difference. The analyses were performed using R v. 3.3.1 and the survival package v. 2.39.4.

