## Background

Hip fractures are a major cause of injury, morbidity and death in older patients. Undisplaced FNF (uFNF) are classified according to the Garden classification system on the anteroposterior X-ray [1, 2]. The routine surgical procedure for uFNFs, regardless of the patient’s age, is internal fixation (IF) with 2–3 screws or pins. Advanced age has been described as a risk factor for healing complications in uFNFs [3, 4]. In older patients reoperation rates ranging between 8 and 21% have been reported in the literature [2, 5–7]. In older patients displaced FNFs are treated with hip arthroplasty, which produces better and more predictable results compared with IF [5]. The reoperation rate for hemiarthroplasties for displaced FNFs is lower than for undisplaced fractures that are operated with IF [5, 8, 9]. A randomised controlled trial (RCT) comparing modern hemiarthroplasty with screw fixation for uFNFs found no significant difference in hip function but hemiarthroplasty led to improved mobility and fewer major reoperations [8].

In the Swedish Fracture Register (SFR) all fracture types in adults and all long-bone fractures in children are registered [10]. The SFR is a unique national quality register as it contains information on fractures, regardless of treatment (surgical or non-surgical). Seventy-five per cent of the hospitals in Sweden that manage fractures on a regular basis participate in the SFR.

A question often arises as to whether the results from an RCT can be extrapolated from the study environment to a general health care setting [11, 12]. Active participation of patients and recruitment of large sample sizes in an RCT are not easily achieved and refusal to participate and loss to follow-up (a form of selection bias) are prevalent problems. Conducting register-based RCTs (rRCTs), which include a randomisation module in a large, all-inclusive clinical register with unselected consecutive enrolment, can combine some of the most important features of a prospective randomised trial with the inclusiveness and efficiency of a large-scale clinical register. The consecutive enrolment in combination with patient identification and automated linked register-based follow-up allows for a cost-effective model with analysis of those who are lost to follow-up [13].

There are limited data comparing IF and hip arthroplasty for uFNF fractures and trials have been called for to optimise the surgical treatment [2, 14].

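### The 27.5% and 22.5% composite rates count patients who are reoperated and die twice, so the stated 80% power holds only if no reoperated patient dies within the year

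*Protocol article*

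**What the plan says.** All the planning figures are in the protocol article, section Estimated sample size and power.

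- Mortality: "we expect a 15% 1-year mortality within the study cohort". It is chosen from a reported range: "Mortality rates are reported from 11% at 1 year in a study with both displaced and undisplaced FNFs", up to just over 20% in other studies.
- Reoperation after internal fixation (IF): "we estimate that the rate is about 12.5% at 1 year after IF with screws/pins in older patients with uFNF". For arthroplasty, 7.5% is assumed.
- Composite, control arm: "death or reoperation would occur within 1 year in 27.5% (15% + 12.5%) of the patients in the control group (IF").
- Composite, intervention arm: "aim to detect a decrease to 22.5% (15% + 7.5%) in the intervention group (arthroplasty").
- Result: "Simulations under an assumption of constant hazard" give 1440 patients over 3 years, "yielding about 586 events, would produce a power of 80% to detect such a difference".

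The section Statistics analyses the composite as time to first event by Cox regression adjusted for age.

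**The concern.** The probability of death or reoperation equals the sum of the two probabilities only if no patient has both. The 15% is given as mortality in the whole cohort, not as death without reoperation. A patient who is reoperated in month 3 and dies in month 9 is therefore in both terms of the sum, yet supplies one first event to the analysis.

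If the risk of death after reoperation is similar in the two arms, more patients are double-counted under IF (12.5% reoperated) than under arthroplasty (7.5%). The sums then overstate both the number of events and the difference between arms, and both errors raise the calculated power. The event count and the 80% are the stated justification for 1440 patients.

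**Working it through.** **Inputs.** From the protocol article: 15% mortality, 12.5% and 7.5% reoperation, 1440 patients, 3 years' inclusion, follow-up of at least 1 year and capped at 2 years, constant hazard. Assumed because not stated: uniform accrual, 1:1 allocation, two-sided 5%.

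**Formulas.**
- Hazard from a 1-year rate p: λ = −ln(1 − p).
- Event probability per patient: (2/3)(1 − e^(−2λ)) plus (1/3) times the mean of 1 − e^(−λt) for t uniform on 1 to 2 years.
- Power (Schoenfeld): Φ(√(D/4)·|ln HR| − 1.96), with D the expected events.

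**Step 1. The stated figures.**
- λ(IF) = −ln 0.725 = 0.3216; λ(arthroplasty) = −ln 0.775 = 0.2549; HR = 0.793.
- Events: 720 × 0.4429 + 720 × 0.3716 = 318.9 + 267.5 = 586.4.
- Power: Φ(2.814 − 1.96) = 80.3%.

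Both 586 and 80% reproduce, so the simple sums are consistent with what was simulated.

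**Step 2a. Overlap removed, 12.5% and 7.5% read as crude 1-year proportions.** Take the death hazard h_D = −ln 0.85 = 0.1625, the same before and after reoperation. Solve h_R/(h_R + h_D) × (1 − e^(−(h_R + h_D))) = 0.125 or 0.075.
- h_R = 0.1452 (IF) and 0.0847 (arthroplasty).
- Composite: 1 − e^(−0.3077) = 26.5%; 1 − e^(−0.2472) = 21.9%.
- HR 0.803; events 308.8 + 261.1 = 569.9; power Φ(2.616 − 1.96) = 74.4%.
- Implied overlap: 27.5 − 26.5 = 1.0 point and 22.5 − 21.9 = 0.6 point, about 8% of reoperated patients in each arm.

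**Step 2b. Overlap removed, rates read as net and independent of death.**
- Composite: 1 − 0.85 × 0.875 = 25.6%; 1 − 0.85 × 0.925 = 21.4%.
- HR 0.812; events 300.0 + 255.5 = 555.5; power Φ(2.450 − 1.96) = 68.8%.

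**Step 2c. Overlap set directly.** Let a fraction f of reoperated patients die within the year, equal in both arms (assumption). The composite is 15% + 12.5%(1 − f) vs 15% + 7.5%(1 − f).

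| f | IF vs arthroplasty | HR | Events | Power |
|---|---|---|---|---|
| 0 | 27.5% vs 22.5% | 0.793 | 586 | 80.3% |
| 5% | 26.9% vs 22.1% | 0.799 | 576 | 76.9% |
| 10% | 26.25% vs 21.75% | 0.806 | 566 | 73.0% |
| 20% | 25.0% vs 21.0% | 0.819 | 545 | 64.3% |

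**Check.** Log-rank simulations of 20,000 trials each gave 80.2% for the stated rates, 74.4% for step 2a and 68.7% for step 2b.

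**The case against.** **The 80% is not a miscalculation.** This stands. It follows from the stated inputs, which the article labels as assumptions. What is wrong is how two of those inputs, the composite rates, were formed from the rates the article itself chose.

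**The overlap is unknown.** This also stands: no figure is given for deaths among reoperated patients, and the net reading behind 69% is not stated in the article. Nor must overlap always cost power. One point in each arm (26.5% vs 21.5%) gives HR 0.786, 566 events and 81.6%. But that needs 1/7.5 = 13.3% of reoperated arthroplasty patients to die, against 1/12.5 = 8.0% of reoperated IF patients, and nothing in the article suggests such a gap.

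**The inputs are uncertain anyway.** On the crude reading, power is about 82% at 11% mortality and 66% at 20%; under independence it is 78.5% and 57.7%. An arthroplasty reoperation rate of 7.0% instead of 7.5% gives about 82% on the crude reading. This is true, but the overlap loss comes on top: at 11% and 20% mortality the simple sums give 85.6% and 74.8%. Uncertainty about the components does not make their sum the right formula.

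**The 15% might mean death without reoperation.** The sum would then be correct, but the text presents it as mortality in the cohort and draws it from reported mortality rates.

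**A stronger reading on year 2.** A reader might infer that constant hazard contradicts the Background, which says: "In older patients reoperation rates ranging between 8 and 21% have been reported in the literature". Carried to 2 years, the control rate implies reoperation in (12.5/27.5) × (1 − 0.725²) = 21.6%. The quoted range has no time horizon, the excess is 0.6 points, and constant hazard is openly declared, so there is no contradiction. The article also gives no basis for any particular fall in the year-2 hazard, so no power loss can be attached to it.

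**Conclusion.** The composite rates are wrong as formed: they are sums where the probability of either event is needed. The 586 events and 80% power hold only with zero overlap between reoperation and death in the first year. At the protocol's own 15% mortality, with 1440 patients, constant hazard, 1:1 allocation, two-sided 5% and a similar death risk after reoperation in both arms, power is about 74% with 570 events (crude reading) or about 69% with 556 events (independent net rates). The direction is clear under those assumptions; the size is a range that the documents do not settle.

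A reader might go further and conclude that the trial is too small or that its analysis is compromised. That does not follow. The primary analysis is unaffected, and the result will be judged on the hazard ratio and its confidence interval. What needs correcting is the claim about the difference the trial can detect with 80% power.

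**What to change.** In the section Estimated sample size and power:

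1. Replace the sums with the probability of death or reoperation net of overlap: about 26.5% vs 21.9%, or 25.6% vs 21.4% under independence. State which reading of 12.5% and 7.5% is meant and what overlap is assumed.
2. Re-run the simulation with separate hazards for death and reoperation, and restate expected events and power (about 69–74%). Constant hazard can be varied in the same run as a declared assumption.
3. Alternatively, keep the present design statement but tie the 80% to a hazard ratio of about 0.79 with about 586 events, and no longer present it as the power for the stated mortality and reoperation rates.

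The cost is one re-run of an existing simulation and a reworded paragraph. Under the first route the stated power becomes less favourable. Sample size, endpoint and analysis stay as they are.

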### Statistics

Time to first event will be presented as Kaplan-Meier plots. The primary composite and the individual components will be analysed for time to first event using Cox regression adjusted for age as a linear covariate and presented as hazard ratios with 95% confidence intervals and *p*-value. Because of the register follow-up, we assume that follow-up will be complete. In the rare event that a patient is known to have incomplete follow-up, the patient will be considered censored at the last known follow-up. For the reoperation endpoint, death will be handled as censoring events.

The number of patients with a perioperative event and event within 2 years will be summarised in tables. Patients lost to follow-up will be included in the denominator, and the 2-year frequencies will only include patients randomised at least 2 years before data collection. Supplementary sensitivity analyses will include analyses censored at 1 year and analyses of the number of patients with events within 2 years. Secondary outcomes will be presented in the same way as the primary composite and its components.

Statistical expertise at the Uppsala Clinical Research Center will perform the statistical analyses. Data will be blinded for the principal investigators until the final analysis has been performed and until the writing of the manuscript.

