### Outcome measurements

#### Primary endpoint

The primary outcome of this rRCT will be a composite variable (reoperation rate and mortality). Arthroplasty is a more elaborate surgical procedure that might affect peri- and postoperative short-term mortality, as related to longer operating times, higher blood loss, and the occurrence of bone cement implantation syndrome. A higher mortality in one study group would affect the reoperation rate in that group. Therefore, we decided to construct a composite variable as the primary outcome. There will be no formal follow-ups in addition to the local clinical routines. Data on mortality and reoperations are registered in the National Patient Register (NPR) (all codes for procedures and diagnoses from hospitals), the Swedish Hip Arthroplasty Register (SHAR) (change of implant, reoperation due to dislocation, fracture or infection) and in the SFR (fracture close to implant, removal of pins/screws, conversion to arthroplasty).

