#### Secondary endpoints

Secondary endpoints will include reoperation rate and mortality as stand-alone variables.

PROM, as measured by the Short Musculoskeletal Functional Assessment (SMFA) questionnaire [15], will be routinely collected within the SFR 1 year after the injury and compared with the results obtained by recall technique at the time of the fracture. No additional PROMs will be collected.

Other secondary endpoints will include the occurrence of adverse events defined as suffering, physical harm or disease, as well as death related to the index admission and as a condition that was not an inevitable consequence of the patient’s disease or treatment. The external validity of the trial will be evaluated by comparing the outcome between those who were included in the rRCT with those who fulfilled the inclusion criteria but declined to participate.

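### Short-term mortality is the harm named for arthroplasty, but the mortality estimate stated with an interval is a hazard ratio over up to 2 years (1 year as sensitivity), which has little power for an early excess

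*Protocol article*

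**What the plan says.** All references are to the protocol article.

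- **Primary endpoint** names the possible harm: "Arthroplasty is a more elaborate surgical procedure that might affect peri- and postoperative short-term mortality". It gives longer operating time, blood loss and bone cement implantation syndrome as reasons.
- **Statistics** fixes the analysis of the composite and of mortality alone: "The primary composite and the individual components will be analysed for time to first event using Cox regression adjusted for age". Results are hazard ratios with 95% confidence intervals and p-values.
- **Statistics** also plans other outputs: "Time to first event will be presented as Kaplan-Meier plots"; "The number of patients with a perioperative event and event within 2 years will be summarised in tables"; "Supplementary sensitivity analyses will include analyses censored at 1 year and analyses of the number of patients with events within 2 years".
- **Secondary endpoints** defines adverse events to include early deaths of one kind: "as well as death related to the index admission". Statistics adds: "Secondary outcomes will be presented in the same way as the primary composite and its components".
- **Data collection and follow-up** sets the register linkage: "Follow-up will be performed postoperatively after 2, 5, and 10 years by linking between the registers".

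No day limit is given for a perioperative event. No estimate of all-cause death within a fixed early window is stated.

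**The concern.** Harm from the operation itself would be expected to fall in the first days or weeks. Later deaths in patients aged 75 and over come largely from age and frailty and would be similar in both arms. The hazards would then not be proportional. A single hazard ratio over up to 2 years averages a short period of excess with a long period of none, and most of the deaths come from the long period.

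The abstract's Discussion says the trial could shift practice towards arthroplasty. A non-significant mortality hazard ratio near 1.1 could then be read as reassurance about operative risk, a question on which that estimate says little.

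**Working it through.** **1. The plan's own figure.** The inputs are in the sample size section: composite rates at 1 year of 27.5% and 22.5%, 1440 patients, 3-year accrual, and follow-up of 1 to 2 years. Two-sided alpha of 0.05 and 1:1 allocation are assumed, as neither is stated.

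- HR = ln(1 − 0.225) / ln(1 − 0.275) = 0.793.
- With constant hazards and 720 per arm, expected events are 586.4 and power is 80.3%. This reproduces the stated 586 events and 80%.

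**2. Mortality alone under a constant effect.** With 15% 1-year mortality in both arms, about 370 deaths are expected. The HR needed for 80% power is exp(2 × (1.96 + 0.84) / √370) ≈ 1.34.

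**3. Mortality when the harm is early, worked for 5% versus 8% at 30 days.** These two rates are assumptions. Hazards are taken as equal after day 30.

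- Early HR = ln(0.92) / ln(0.95) = 1.63, so ln HR = 0.486.
- Deaths by day 30: 720 × (0.05 + 0.08) = 93.6.
- Later hazard, set so that control mortality is 15% at 1 year: (0.1625 − 0.0513) / (1 − 30/365.25) = 0.121 per year.
- Survivors at day 30: 720 × (0.95 + 0.92) = 1346. Their chance of a later observed death is 0.207 for the two thirds followed to 2 years and about 0.157 for the rest, 0.191 on average. That gives about 257 deaths, and about 350 in all.
- Average ln HR ≈ (93.6 / 350) × 0.486 = 0.130, so HR ≈ 1.14.
- Power to 2 years: z = 0.130 × √(350/4) = 1.22; Φ(1.22 − 1.96) ≈ 23%.
- Censored at 1 year: later deaths are 1346 × 0.105 ≈ 142, total about 235. Average ln HR = (93.6 / 235) × 0.486 = 0.193; z = 0.193 × √(235/4) = 1.48; power ≈ 32%.
- 30-day comparison of proportions: SE = √(0.05 × 0.95/720 + 0.08 × 0.92/720) = 0.0130; z = 0.03 / 0.0130 = 2.31; power ≈ 64%.

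**4. Simulation over a range of assumed 30-day rates.** There were 4000 trials per row (2000 for 4% vs 7%). The test is the log-rank test, which is the score test of the unadjusted Cox model. Power is for z > 1.96 in the direction of harm.

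| IF vs arthroplasty at 30 days | Average HR to 2 years | Power, to 2 years | Power, censored at 1 year | Power, 30 days |
|---|---|---|---|---|
| 3% vs 5% | 1.08 | 12% | 16% | 51% |
| 4% vs 6% | 1.08 | 11% | 16% | 40% |
| 5% vs 7% | 1.09 | 13% | 17% | 36% |
| 3% vs 6% | 1.13 | 21% | 31% | 79% |
| 4% vs 7% | 1.13 | 20% | 31% | 71% |
| 5% vs 8% | 1.14 | 23% | 31% | 64% |

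Repeat runs differ by a point or two, so the ranges are about 11–23%, 16–32% and 35–80%.

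**5. Sensitivity.**

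- The article reports 1-year mortality from 11% to just over 20%. At 11% or 20%, 4% vs 6% gives 15% or 10% power to 2 years, and 42% at 30 days.
- A harm spread over 90 days (7% vs 10%) gives 23% to 2 years, 31% at 1 year and 54% for a 90-day comparison.
- Only a doubling from 5% to 10% at 30 days brings the 2-year analysis to about 51%; the 30-day comparison then has 95%.

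**The case against.** The strongest case on the other side has five parts.

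- **The hazard ratio does not stand alone.** A reader might infer that it is the only look at mortality and that early harm would go unseen. The article does not support that. It plans plots, a perioperative table, a 1-year analysis, 2-year counts and index-admission deaths within a secondary endpoint. That endpoint may itself receive a hazard ratio and interval, since secondary outcomes are to be presented like the primary. This stands. However, death related to an admission needs a judgement of relatedness in an unblinded trial and has no fixed time limit. The perioperative table is a count with no stated window, and a plot gives no stated estimate of an early difference.
- **The composite was built for another reason.** Its stated rationale is that a mortality difference would distort the reoperation rate. The Discussion also cites a trial with higher mortality after IF. Both are true: the article poses no formal early-safety hypothesis, and the direction is uncertain. An early estimate would inform either direction.
- **The 2-, 5- and 10-year times might be read as the only windows possible.** They are dates of register linkage and do not limit what can be analysed.
- **Such detail belongs in an analysis plan, which is not shown.** That is partly fair. But the article itself fixes the model, the covariate, the effect measure and the sensitivity windows, and this choice fits its own stated risk poorly.
- **The effects are assumed, and a 30-day comparison is not strong either.** This stands. For a 2-point excess it misses in about half of trials or more, so part of the low power is sample size.

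**Conclusion.** The point holds as a mismatch between the named risk and the stated mortality estimate. The Cox model is not wrong, and neither the primary analysis nor the sample size is affected. A 3-point 30-day excess, about 22 extra deaths among 720 patients (0.03 × 720 = 21.6), would be missed by the 2-year hazard ratio in about four of five trials and by the 1-year analysis in about two of three.

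The conclusion rests on assumed 30-day rates, equal hazards after the early window, 1:1 allocation, two-sided 5% significance and no age adjustment in the simulation. If deaths were merely brought forward, the 2-year hazard ratio would be diluted further.

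The article does not support saying that the safety question would go unanswered. It supports saying that no planned output is stated to estimate all-cause death in a fixed early window with an interval.

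**What to change.** In Secondary endpoints and Statistics:

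- Name all-cause mortality within 30 days and within 90 days of randomisation, by allocated arm, as a secondary safety outcome.
- Report each for all randomised patients as a risk difference with 95% CI, beside the overall Cox hazard ratio, which stays as it is.
- State that a non-significant 2-year hazard ratio will not be read as excluding early harm.
- Omit a hazard ratio for the period after 90 days, or label it descriptive. It compares survivors only and is not protected by randomisation if early deaths differ.

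The cost is some wording, a few table rows and two more secondary estimates. Death dates are already needed for the primary outcome, and planned follow-up is at least 1 year for every patient.

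The interval will still be wide for a small excess. For 4% versus 6%, the half-width is 1.96 × √(0.04 × 0.96/720 + 0.06 × 0.94/720) ≈ 2.2 points, so an observed 2-point difference would have an interval that just includes zero. That is a reason to report the interval and not rely on a p-value.

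### The Kaplan-Meier curve implied for reoperation, with death censored, overstates the proportion of patients reoperated; cumulative incidence should be shown instead

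*Protocol article*

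**What the plan says.** Under Secondary endpoints: "Secondary endpoints will include reoperation rate and mortality as stand-alone variables".

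The Statistics section sets the display: "Time to first event will be presented as Kaplan-Meier plots". It then fixes the model for the composite and its parts: "The primary composite and the individual components will be analysed for time to first event using Cox regression adjusted for age as a linear covariate". For reoperation it adds: "For the reoperation endpoint, death will be handled as censoring events". The remaining outcomes follow suit: "Secondary outcomes will be presented in the same way as the primary composite and its components". No cumulative incidence function or other competing-risk estimate is named.

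The same section also tabulates the number of patients with an event within 2 years, restricted to patients randomised at least 2 years before data collection, and uses such counts in a sensitivity analysis.

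Under Primary endpoint, the composite is justified by the interplay of the two components: "A higher mortality in one study group would affect the reoperation rate in that group".

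Under Estimated sample size and power: "Patients will be censored at the time of reoperation or at time of death within 2 years".

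**The concern.** When death is censored, one minus Kaplan-Meier estimates the probability of reoperation in a hypothetical population in which nobody dies. In this cohort death is common and patients who die cannot be reoperated, so the curve lies above the proportion of patients who are in fact reoperated. The excess is larger in points in the arm with more reoperations, so an arm difference read from the curves is inflated in favour of arthroplasty. The protocol's own reason for a composite is that mortality and reoperation cannot be read apart from each other, and the implied curve sets that aside.

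A smaller matter is the sample-size sentence. It calls reoperation and death censoring, although they are the events of the composite, and it does not say that stand-alone mortality continues to be followed after a reoperation.

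**Working it through.** **Inputs** (Estimated sample size and power): one-year proportions of 15% death + 12.5% reoperation = 27.5% for internal fixation (IF) and 15% + 7.5% = 22.5% for arthroplasty; constant hazard; 1440 patients over 3 years; follow-up ending 1 year after the last patient and capped at 2 years. Assumed here: 1:1 allocation, uniform accrual, two-sided 5% level.

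**1. Reproduce the plan's figure.** Total hazards are −ln(0.725) = 0.3216 and −ln(0.775) = 0.2549, a hazard ratio of 0.793. Two thirds of patients have 2 years of follow-up and one third between 1 and 2 years.
- IF: 720 × [2/3 × 0.4744 + 1/3 × 0.3800] = 318.9 events.
- Arthroplasty: 720 × [2/3 × 0.3994 + 1/3 × 0.3159] = 267.5 events.
- The total is 586.4, against about 586 stated. Schoenfeld power is 80.3%, against 80% stated. The hazards used below are therefore the plan's own.

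**2. Split each hazard by cause** in the stated proportions.
- IF reoperation: 0.3216 × 12.5/27.5 = 0.1462; death 0.1754.
- Arthroplasty reoperation: 0.2549 × 7.5/22.5 = 0.0850; death 0.1699.

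**3. Two-year reoperation by each estimator.** One minus Kaplan-Meier is 1 − exp(−2 × reoperation hazard). Cumulative incidence is the reoperation share × [1 − exp(−2 × total hazard)].
- IF: 1 − exp(−0.2923) = 25.3%, against 0.4545 × 0.4744 = 21.6%. Excess 3.8 points.
- Arthroplasty: 1 − exp(−0.1699) = 15.6%, against 0.3333 × 0.3994 = 13.3%. Excess 2.3 points.
- Arm difference: 9.72 against 8.25 points, a ratio of 1.18.

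**4. Additivity.** The plan adds the components to obtain the composite, which works only for cumulative incidences. At 2 years in the IF arm, reoperation 21.6% plus death as first event 25.9% gives the composite 47.4% (after rounding). With the Kaplan-Meier figure, 25.3% + 25.9% = 51.2%, which does not match.

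**5. Sensitivity to hazard shape.** The cumulative reoperation hazard is taken as Weibull with a constant death hazard, recalibrated to the same one-year proportions. The shapes are assumptions; 1.0 is the constant-hazard case. Figures are two-year percentages, one minus Kaplan-Meier / cumulative incidence, with arm differences in points.

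| Shape | IF | Arthroplasty | Arm difference |
|---|---|---|---|
| 0.4 | 16.9 / 15.4 | 10.2 / 9.3 | 6.7 / 6.1 |
| 0.6 | 19.5 / 17.2 | 11.8 / 10.5 | 7.6 / 6.7 |
| 0.8 | 22.3 / 19.3 | 13.6 / 11.8 | 8.6 / 7.5 |
| 1.0 | 25.3 / 21.6 | 15.6 / 13.3 | 9.7 / 8.25 |

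The excess shrinks to 1.5–3.0 points (IF) and 0.9–1.8 points (arthroplasty) for shapes 0.4–0.8, but does not vanish.

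**6. Mortality, if follow-up were stopped at reoperation.** In a simulation on the hazards of step 2, with the death hazard unchanged by reoperation, the mortality hazard ratio is 0.967 when censored at reoperation and 0.968 with full follow-up, although about 352 rather than 389 deaths are counted. If reoperation is assumed to double the death hazard, the two are 0.968 and 0.931. The documents give no figure for such an effect.

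**The case against.** **The Cox analysis is sound.** Censoring death in a Cox model for reoperation gives the standard cause-specific hazard ratio, which is the only effect measure specified for the components. This stands; the point concerns the absolute-risk display alone.

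**The reoperation curve is implied, and other figures avoid the bias.** No sentence says outright that reoperation will have a Kaplan-Meier plot, and no risk difference from such a plot is planned. The crude 2-year frequencies are free of this bias. All of this is correct. But the Statistics section, read as a whole, leads to that plot. The crude frequencies cover only patients randomised at least 2 years earlier, about two thirds by the plan's own account. A report could then carry two different 2-year reoperation figures with no rule on which to quote.

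**The size depends on constant hazards.** It does, and step 5 gives the smaller range.

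**A stronger reading on mortality.** A reader might infer from the sample-size sentence and the phrase about first events that deaths after reoperation will be dropped, and that this creates a false mortality excess for arthroplasty. With a common death hazard of −ln(0.85) = 0.1625, deaths as first event come to 24.3% (IF) and 25.6% (arthroplasty), which looks like such an excess. The documents do not support this:
- The sentence sits in the paragraph on the composite, where stopping at the first event is right. No section stops mortality follow-up at reoperation, mortality is listed as a stand-alone endpoint, and the only competing-event rule given is for reoperation.
- Those percentages are cumulative incidences of death as first event, which the plan does not propose to report. Under the same assumption the planned Cox hazard ratio would be 1 and one minus Kaplan-Meier would be 27.75% in both arms.
- The assumed hazards do not fit the plan: 0.1625 + 0.1462 = 0.3087 gives a one-year IF composite of 26.6%, not 27.5%. On the plan's split the first-event figures are 25.9% and 26.6%.

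**Conclusion.** The point holds for the absolute risk of reoperation. On the plan's rates and constant hazards, the implied curve overstates two-year reoperation by 3.8 points after IF and 2.3 points after arthroplasty (about 17% in relative terms), and the arm difference by about 1.5 points. With front-loaded reoperations the overstatement is smaller but in the same direction. The result rests on the stated one-year proportions being first-event proportions, as their addition implies, and on the Kaplan-Meier plot being meant for reoperation as well.

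This affects the display of one secondary endpoint. The primary composite, its sample size and its power are not touched, and the cause-specific hazard ratio for reoperation is valid. The mortality wording is an ambiguity to close and not a demonstrated bias: the mortality hazard ratio would be biased only if follow-up were stopped at reoperation and reoperation also changed the death hazard.

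**What to change.** - **Reoperation:** plot and report Aalen-Johansen cumulative incidence by arm, with death as a competing event, in place of a Kaplan-Meier curve. This uses all patients, including those with 1 to 2 years of follow-up. Keep the age-adjusted Cox hazard ratio and label it cause-specific. A Fine-Gray model is optional.
- **Sample-size section:** reword so that reoperation and death are events of the composite. Only withdrawal of consent, the 2-year limit and the end of the study (or last known follow-up) should censor.
- **Mortality:** state that each patient is followed to death or cut-off regardless of reoperation.

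The cost is a few sentences in the protocol or analysis plan and a few lines of code. The registers already supply both outcomes, so no new data are needed.
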